### Process evaluation

Data for the process evaluation will be collected continuously throughout the study and as part of the telephone interviews at both measurement points (T_0_, T_1_) to investigate the process evaluation domains of *reach, fidelity, dosage,* and *context* [47, 48]. Different data sources will be used to evaluate the recruitment and intervention process (see Table 1).

Within the *reach* domain, variables reflecting the recruitment process, like the recruitment strategy, the numbers of interested, refused, rejected, and included individuals, the randomization, and the number and reasons for dropouts, will be collected. Intervention *fidelity* will be assessed with single items during the telephone interviews at the T_1_ measurement point. The single items reflect, e.g., the quality of the moderator, the information booklet, the preparatory calls, the group process, schedule difficulties, and technical problems during the telephone-based support groups. Moreover, the structured evaluation of each support group session (questionnaire) by each study participant is one further potential data source for the investigation of intervention fidelity.

The intervention *dosage* will be investigated based on data on the adherence to the protocol and actual attendance of the informal caregivers. These data will be collected with standardized protocols for each support group session completed by the moderator and single items rated during the telephone interviews.

The *context* of the intervention implementation will be evaluated using the data on the characteristics of the study participants and their care recipients. Moreover, the use and non-use of health care services and the associated reasons for their use or non-use will be assessed with the standardized use of service checklist [49]. The checklist contains 24 items and was developed as part of the European Actifcare study. Each of the items can be answered based on 12 different response options reflecting the use and non-use and associated reasons [50].

## Data analysis

### Effect analysis

The primary and secondary outcomes from the intervention and control groups will be compared using descriptive and advanced statistical methods at T_0_ and T_1_. A mixed effect model will be computed to evaluate the differences between the intervention and control groups regarding the development of primary and all secondary outcomes during the study period (T_1_). The mixed effect model will account for the repeated measurements of the participants. Additionally, a model for evaluating the impact of the between cluster differences will be tested by including the clusters as random effects. A cluster is defined as a group of a maximum of four informal caregivers who represent the members of one support group. To evaluate the effect of the assignment, the intention to treat principle (ITT) will be applied. The results of the ITT will be compared to a per protocol analysis to assess the effect of intervention adherence. In all analytical steps, the effect estimates will be adjusted for baseline differences and differences in the control variables at all measurement points. The mixed effect model for the primary outcome will also consider the secondary outcomes as control variables. A statistician who is blinded to group allocation will perform the statistical analyses. The research team members responsible for the effect evaluation will be blinded to the results of the process evaluation until the final mixed effect model for the primary outcome is computed.

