## Methods/Design

### Design

The evaluation of the TALKING TIME intervention is based on data of a two level design, where informal caregivers are nested within groups of eight persons. Informal caregivers will be randomized within a group into support and control group, four informal caregivers each (Fig. 2). Measurements are assessed at two measurement points resulting in repeated measurements of informal caregivers (Fig. 1). Computer-generated randomization lists will be used. The randomization will be performed by an external data manager who will not be involved in the study intervention or data analysis. Only the team performing the intervention will be informed of the group assignments. The statistician and researchers responsible for data collection will be blinded regarding the group assignments. The inclusion criteria and baseline data of the study will be assessed before the randomization of participants.

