### Sample size calculation

The sample size calculation is based on the effect size of the primary outcome, the “mental component” of the HRQoL. A meta-analysis demonstrated an effect size of 2.03 (95% Confidence Interval 1.36 to 2.70) for SWB in support groups but only measured in one single trial [6]. We assume a more conservative effect size of 0.70. This effect size was chosen on the basis of the findings of the study „German Adaptation of REACH II“(GE-REACH) [28], which yielded an effect size between 0.57 (post) and 0.89 (follow-up), thus on average 0.73, for the outcome SWB, measured with mental component summary (MCS) of the General Health Survey Questionnaire Short Form 12 (SF-12). The randomization will be performed on the individual participant level within predefined clusters; a conservative sample size calculation based on a parallel design is computed. A significance level of α of 0.05 (two sided) and a power of 80% for psychological QoL results in a target sample size of 68 participants (34 in each group). An estimated dropout rate of 20% [29] will raise the sample size to 86 study participants. The clusters with eight informal caregivers each lead to a further increase of the sample to 88 informal caregivers (eleven clusters with eight participants each). Therefore, we plan to include 88 informal caregivers in the TALKING TIME study.

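### Cluster means eight caregivers in the design and at most four in the analysis, and the first-named model contains neither unit, so the standard error of the treatment effect can be wrong in either direction

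*Protocol article*

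**What the plan says.** The Design section describes a two-level structure "where informal caregivers are nested within groups of eight persons", each group being randomised four to support and four to control. The Sample size calculation uses the same unit, "eleven clusters with eight participants each", and states that "a conservative sample size calculation based on a parallel design is computed".

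The Effect analysis section first names a mixed model that accounts for the repeated measurements of each participant. It continues: "Additionally, a model for evaluating the impact of the between cluster differences will be tested by including the clusters as random effects". It then defines the unit: "A cluster is defined as a group of a maximum of four informal caregivers who represent the members of one support group". The group of eight does not appear in that section.

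The Control group section says that controls receive no component of the intervention until after T1. The Intervention section gives each support group one moderator and six shared sessions.

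**The concern.** One word names two units. The group of eight is the randomisation block and spans both arms. The support group of four is the unit of delivery, and during the comparison only the intervention arm shares one. The random effect planned in the analysis uses the second meaning, and the text does not say how controls are coded for it.

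The two units affect the standard error in opposite ways. Caregivers who share a moderator and six sessions may have correlated T1 outcomes, and treating them as independent understates the variance. Blocks that differ from one another add variance that cancels out of the within-block comparison, and leaving them out overstates the standard error. The first-named model has neither term. The article also refers to a final mixed model for the primary outcome without saying which of the two models that is. The confidence interval and p-value for the SF-12 mental component summary (MCS) depend on that choice.

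**Working it through.** **1. The plan's own figure.** Inputs from the Sample size calculation: effect size 0.70, two-sided α 0.05, power 80%, dropout 20%. For a two-sample t-test, noncentral-t power is 79.97% at 33 per arm and 81.2% at 34 per arm, so 34 per arm (68) is right. Dropout: 34/0.80 = 42.5, rounded up to 43 per arm, gives 86. Whole groups: 86/8 = 10.75, rounded up to 11, gives 11 × 8 = 88. All three figures reproduce. None contains an ICC or a design effect.

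**2. Support-group correlation alone.** The article gives no ICC, so 0.05, 0.10 and 0.20 are assumed. Group size after dropout is m = 34/11 = 3.09 with 34 per arm, or 4 × 0.80 = 3.2 with about 35 per arm.

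- Design effect, intervention arm only: DE = 1 + (m − 1) × ICC
- Variance factor for the difference: (DE + 1)/2; true-to-naive SE ratio = √[(DE + 1)/2]
- Actual error of the unclustered test: 2 × [1 − Φ(1.96/SE ratio)]
- Power: noncentral t with 2n − 2 df and noncentrality 0.70/√[(DE + 1)/n]

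Example with m = 3.2, ICC = 0.10, n = 35: DE = 1 + 2.2 × 0.10 = 1.22; factor 1.11; SE ratio 1.054; error 2 × [1 − Φ(1.860)] = 6.3%; noncentrality 0.70/√(2.22/35) = 2.78; power 78.2%.

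| ICC | DE | SE ratio | Two-sided error | Power, 34-35 per arm |
|---|---|---|---|---|
| 0 | 1.00 | 1.00 | 5.0% | 81-82% |
| 0.05 | 1.10-1.11 | 1.03 | 5.6% | 79-80% |
| 0.10 | 1.21-1.22 | 1.05 | 6.2-6.3% | 77-78% |
| 0.20 | 1.42-1.44 | 1.10-1.11 | 7.5-7.6% | 73-74% |

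Power here uses the correct variance but no baseline adjustment and no small-sample df penalty.

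**3. Omitted blocks alone.** With equal arms inside each block and block ICC b, the true variance of the difference is (1 − b) times what the naive model assumes. At b = 0.10 the SE ratio is √0.90 = 0.949 and the error is 2 × [1 − Φ(1.96/0.949)], about 3.9%.

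**4. Both together.** Simulation of 11 blocks of eight, four per arm, 20% random dropout, T1 outcomes compared by an ordinary t-test. There were 6,000 runs per cell, so the simulation error is about √(0.05 × 0.95/6000) = 0.3 percentage points.

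| Support-group ICC | Block ICC 0 | Block ICC 0.05 | Block ICC 0.10 |
|---|---|---|---|
| 0 | 5.1% | 4.6% | 4.0% |
| 0.05 | 5.3% | 5.4% | 4.9% |
| 0.10 | 6.6% | 5.6% | 5.5% |
| 0.20 | 7.5% | 6.8% | 7.0% |

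Independent repeats gave up to 4.4% in the lowest cell and 7.6% to 8.0% in the highest.

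**5. Does the definition matter?** If *cluster* is read as the eight and only a block effect is fitted, the simulated error over block ICC 0 to 0.10 is 5.7-6.4%, 6.4-6.6% and 7.6-8.7% at support-group ICC 0.05, 0.10 and 0.20. A block effect shared by both arms cannot absorb correlation that exists in one arm. The two definitions therefore give different standard errors.

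**The case against.** Four points can be made for the plan.

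*Clustering is planned for.* A reader might infer that support groups are ignored. They are not: a model with clusters as random effects is announced. What stands is that it is a side model, and that the decisive model is not identified. A reader might also take the word *tested* to mean that the cluster term is dropped when it is not significant. The article states no such rule.

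*The direction of the error is unknown.* It is tempting to say that the type I error exceeds 5%. The tables do not support this as a general statement, because the two omissions partly cancel. At 0.10 for both correlations the simulated error is 5.5%. This objection stands. It does not rescue the plan, because the cancellation depends on two unknown correlations that happen to balance.

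*The sample size may still be adequate.* The calculation leaves out the baseline adjustment that the analysis plans. If the T0-T1 correlation is ρ and adjustment leaves the group variance unreduced, the variance factor becomes (DE + 1)/2 − ρ². The loss is offset when ρ² = (m − 1) × ICC/2. With m = 3.2 this gives ρ = √0.055 = 0.23, √0.11 = 0.33 and √0.22 = 0.47 at the three ICCs. The article gives no ρ, and the small df work the other way, but a claim that the trial is underpowered is not established. The word *conservative* is defensible for stratification and covariate gains. It does not cover group delivery.

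*Controls could be given nominal groups of four*, since they receive the intervention after T1. That is true, but such groups share nothing before T1, and the article does not say that this is how controls will be coded.

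**Conclusion.** The concern holds as a contradiction in the definition of the cluster and as a primary inference that is not fixed. It is more than detail left to an analysis plan: followed as written, the first-named model omits both the unit of delivery and the randomisation block.

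The size is modest and depends on the assumed correlations. The two-sided error is roughly 4% to 7.6%, above 5% when support-group correlation dominates and below it when block differences dominate. The standard error is about 3%, 5% and 10-11% too small at support-group ICC 0.05, 0.10 and 0.20 if blocks do not differ. Unadjusted power stays near 80% at ICC 0.05 and falls to about 73-74% at 0.20.

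These figures treat the comparison as one of T1 means. The ICCs should be read as those of the outcome that the final model analyses. The sample size contains no arithmetic error.

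**What to change.** - Use *block* for the eight and *support group* for the four throughout the document, and state how controls are coded.
- Name one primary model for the MCS: T0 adjustment, arm, a block term in both arms, and a support-group effect in the intervention arm, with small-sample degrees of freedom. For the treatment contrast, a random arm effect by block serves the same purpose. With an unrestricted covariance between the block intercept and the arm effect, the fit does not depend on which arm is coded 1.
- Keep this model whatever the estimated cluster variance. With 11 groups, a test for support-group differences was significant in only 9%, 14% and 32% of simulated trials at ICC 0.05, 0.10 and 0.20, so non-significance says little.
- Qualify *conservative* in the Sample size calculation and report power over a stated ICC range.

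Cost: block and support-group membership are already known from randomisation and delivery, so no new data are needed. The interval widens. With about 10 df the critical value is 2.23 instead of 2.00, about 12% more at the same standard error. In the strictest form, an analysis of the 11 within-block differences without baseline adjustment, simulated power is about 63-77%. An effect confined to the intervention arm reveals which arm is which, so the blinded statistician needs either masked arm codes with the arm-by-block form or a model fit specified in advance.

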The TALKING TIME intervention consists of four fixed components. All components are free of charge and will be implemented as follows:▪ *Component 1*: Telephone-based preliminary talk: To be able to address the concerns of each informal caregiver during the support group sessions (component 3), it is important that the group moderator is aware of the care situation of each individual participating informal caregiver. Therefore, prior to the start of the support groups, the moderator will conduct a preliminary telephone conversation, lasting approximately 30 min, with each informal caregiver. Moreover, the group process, rules of conversation, and a checklist (component 2) are discussed.▪ *Component 2*: Information booklet: To support the thematic introduction of each support group (component 3), each participant will receive an information booklet developed for the TALKING TIME study, summarizing information on the themes (see component 3) of the TALKING TIME sessions and referring to supra-regional contacts and offerings for informal caregivers of people with dementia. The information booklet can be used as a workbook (e.g., for notes) during the support group meeting. The booklet also includes a checklist regarding technical issues (e.g., “what is the battery status of my telephone?”) that must be considered prior to each group session.▪ *Component 3*: Structured telephone-based support groups: Each participant must participate in six telephone-based support group sessions. The support groups are scheduled to occur every two weeks over a three-month period. The groups will consist of a maximum of four informal caregivers and one psychologist who is experienced in working with informal caregivers of people with dementia and who will lead the therapy group as a moderator. The duration of a support group meeting is 60 min. At the beginning of a support group, one of five themes (1. self-care, 2. access to assistance and support offers, 3. communication with healthcare providers (e.g., physicians, qualified nursing staff), 4. communication with family and friends, and 5. improving interaction with the relative with dementia) will be introduced by the moderator. After the thematic introduction, the remaining 45 to 50 min are available for a moderated exchange and discussion among the informal caregivers. At the end of the telephone session, the moderator summarizes the content of the meeting. The content and structure of this telephone-based support group approach are based on the social support component of the caregiver support program Resources for Enhancing Alzheimer’s Caregivers’ Health II (REACH II) [22].▪ *Component 4*: Structured evaluation of each support group session: After each support group session, a structured questionnaire form will be distributed to each support group participant. With this questionnaire, the informal caregivers should individually reflect on each support group session, e.g., “What was good?” “What was my benefit from this session?” “What did I miss, and which questions remain unanswered?” “Which issues do I want to contribute to the next session?”

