
#### Control group

The informal caregivers of the control group receive none of the components of the TALKING TIME intervention during the intervention phase; during this time, they continue with their usual activities or services, without restriction (usual care). However, to motivate these informal caregivers to participate in the data collection, they will receive all of the components of the TALKING TIME intervention after the T_1_ evaluation has occurred.

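### Comparing ITT with per-protocol results does not isolate the effect of adherence; a complier analysis on the same data would be a cheap improvement

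*Protocol article*

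**What the plan says.** The Effect analysis section of the protocol article separates two questions. For the first: "To evaluate the effect of the assignment, the intention to treat principle (ITT) will be applied". For the second: "The results of the ITT will be compared to a per protocol analysis to assess the effect of intervention adherence". It does not say who belongs to the per-protocol set. It adds that in all analytical steps "the effect estimates will be adjusted for baseline differences and differences in the control variables at all measurement points".

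Three other places bear on the point.

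- Control group: "The informal caregivers of the control group receive none of the components of the TALKING TIME intervention during the intervention phase". They are offered it only after T1.
- Intervention group: "Each participant must participate in six telephone-based support group sessions". A preliminary telephone talk and an information booklet are separate components.
- Process evaluation: "The intervention *dosage* will be investigated based on data on the adherence to the protocol and actual attendance of the informal caregivers". On the source: "These data will be collected with standardized protocols for each support group session completed by the moderator".

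The article mentions no complier or instrumental-variable analysis.

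**The concern.** The article goes beyond announcing a per-protocol analysis: it names what the comparison with ITT is meant to show. The comparison does not show that, for two reasons.

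First, attendance exists only in the intervention arm before T1. Excluding poor attenders there, with no matching exclusion among controls, gives up the balance that randomisation provides. If strain or mental health influences who joins the calls, part of the per-protocol difference is selection.

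Second, even without selection, the gap between the two results is not the effect of attending. It is that effect multiplied by the share who did not attend.

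At stake is the interpretation of a supplementary result: the trial could report an adherence effect that is partly, or under a null effect wholly, a product of who chose to attend.

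**Working it through.** **The plan's own figures.** The article gives no adherence rate and no figure for this analysis, so there is none to reproduce. Its sample size does reproduce: a two-sample t-test at effect size 0.70, two-sided 0.05 and 80% power needs 33.02, so 34 per arm (68). 68/0.8 = 85, or 86 as an even total, and 88 in groups of eight. With 20% dropout, 88 × 0.8 = 70.4, so about 35 per arm are evaluable. That number is used below.

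**Algebra.** Let π be the proportion adherent, Δ the effect in adherers, and g the difference in untreated mean outcome, adherers minus non-adherers. With no control access and no effect in non-adherers:

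- ITT = π·Δ
- Per-protocol (adherers against controls) = Δ + (1 − π)·g
- Per-protocol minus ITT = (1 − π)·(Δ + g)
- ITT/π = Δ

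So per-protocol misses Δ by (1 − π)·g. With g = 0, the gap the plan would read is (1 − π)·Δ; at π = 0.8 and Δ = 0.70 this is 0.2 × 0.70 = 0.14, not 0.70.

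**Size without baseline adjustment** (π and g are assumptions). For π = 0.9 to 0.6, the bias is 0.03–0.10 SD at g = 0.25 and 0.05–0.20 SD at g = 0.50. In 20,000 simulated trials per setting, the means matched the formula and ITT/π stayed within 0.01 of the true value.

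**Size with baseline adjustment**, which is closer to the plan. Assume a standard normal trait correlated ρ with MCS at both T0 and T1, attendance by those in the upper fraction π of the trait, no true effect, and T0–T1 correlation r. The unadjusted bias is ρ·φ(c)/π, where c is the attendance cut-off on the trait. At π = 0.6, φ(c)/π = 0.386/0.6 = 0.644; at π = 0.8 it is 0.280/0.8 = 0.350. Attenders differ by the same amount at T0, and adjustment removes about r times that, leaving a factor (1 − r).

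| ρ | π | Unadjusted | Adjusted, r = 0.5 | Adjusted, r = 0.7 |
|---|---|---|---|---|
| 0.2 | 0.6 | 0.129 | 0.064 | 0.039 |
| 0.2 | 0.8 | 0.070 | 0.035 | 0.021 |
| 0.4 | 0.6 | 0.258 | 0.129 | 0.077 |
| 0.4 | 0.8 | 0.140 | 0.070 | 0.042 |

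The adjusted range is therefore 0.02–0.13 SD. Simulation with 35 per arm agrees: the T0-adjusted per-protocol estimate averages 0.02–0.13 SD, with type I error 0.05–0.09, and the T0-adjusted complier estimate averages about 0. The standard deviation of the complier estimate is about 0.22–0.36, against 0.18–0.24 for adjusted per-protocol. These runs treat attendance as yes/no.

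**The case against.** The strongest case on the other side has five parts.

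1. *The plan adjusts for baseline.* A reader might take the unadjusted bias, up to about 0.26 SD, as the size. That does not describe the planned model. Adjustment for T0 removes half or more under the assumptions above, and an analysis of change would remove all of it, because the trait is assumed to act equally at T0 and T1. This stands as a limit on size. It does not remove the problem: bias remains if attendance is related to later change. Adjusting for control variables measured at T1 cannot be relied on to cure it and may add bias.

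2. *Direction is unknown.* A reader might infer a spurious benefit. More strained caregivers could equally attend more, making the bias negative, and with no prognostic gap per-protocol is unbiased for the effect in adherers. This stands.

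3. *The per-protocol set is undefined.* That attenders would be set against all controls is an inference from the controls' lack of access, not a statement in the article. The definition may properly sit in a fuller document.

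4. *Blinding.* Since "A statistician who is blinded to group allocation will perform the statistical analyses", a reader might infer that attendance data would reveal the arm. The same section withholds process-evaluation results from the effect-evaluation team until the final primary model has been computed, and attendance is listed as process data. The document does not support an unblinding concern for the primary result.

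5. *The alternative has its own assumptions.* Caregivers who attend no session may still have had the talk and booklet, so assignment could act other than through sessions. The estimate also needs T1 outcomes from non-attenders, with 20% dropout expected. This stands: the complier effect is identified only under conditions that must be stated.

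**Conclusion.** The point holds in limited form. The stated purpose of the ITT versus per-protocol comparison is not met by that comparison, because attendance can select only within the intervention arm. The comparison is biased whenever attendance is related to prognosis, by an amount and in a direction that the article does not allow anyone to determine. Under a null effect and the assumptions given (60–80% adherence, trait–MCS correlation 0.2–0.4, T0–T1 correlation 0.5–0.7), the T0-adjusted per-protocol estimate is off by about 0.02–0.13 SD.

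This concerns a supplementary analysis; the ITT result is unaffected. A reader might also infer that a wrong adherence effect would set the design of the next trial. The Discussion refers only to the study's findings as a whole, so that goes too far. This is a cheap improvement, not a flaw in the primary analysis.

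**What to change.** Add a complier average causal effect analysis and name it as the estimate of the effect of adherence: two-stage least squares with randomised arm as instrument for the number of sessions attended (0–6; controls 0), adjusted for T0 MCS and randomisation block. Keep the per-protocol result, if wanted, as descriptive only.

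State with it:

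- the exclusion restriction, and that the preliminary talk and booklet strain it;
- the assumption that the effect is linear in sessions attended;
- the need for T1 outcomes from caregivers who attend few or no sessions, which ITT needs as well;
- how grouping within the intervention arm is allowed for.

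The cost is one further analysis on data already being collected, and a wider interval than per-protocol gives, as the standard deviations above show.

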## Background

More than one million people with dementia live in Germany, and it is expected that this number will increase from 1 to 1.5 million currently to 3.0 million people by 2050 [1]. Globally, and particularly in Germany, the family remains the cornerstone of care for older people [2], and therefore, informal (family) caregivers take over much of the responsibility of caring for and supporting people with dementia. More than two-thirds (70%) of care recipients who live at home are cared for predominantly by partners and children [3]. Almost half of these care recipients are also people with dementia [4]. Supporting and caring for people with dementia are time-consuming and are associated with significant personal engagement and day-to-day management. Therefore, informal caregivers of people with dementia often show a higher stress level than that of caregivers of physically frail elderly people [5, 6] and have an increased risk of becoming physically and mentally ill [6]. These negative consequences can be prevented by interventions that improve the individual coping abilities and perceived social support of informal caregivers. The individual and social resources of the informal caregiver are crucial factors that have a moderating influence on the care process and are important components in explaining the association between primary stressors (e.g., support with (instrumental) activities of daily living, emotional support, practical caregiving tasks, challenging behaviors) and secondary stressors (e.g., conflicts between personal needs and care requirements, role conflicts) and the long-term consequences for the health and subjective well-being (SWB) of the informal caregivers [7].

The benefits of psycho-educative interventions, cognitive-behavioral therapy, counseling/case management, general support (e.g., support groups), and respite interventions for informal caregivers of people with dementia with respect to burden and depressive symptoms, ability/knowledge, and SWB have been demonstrated in several studies [6, 8].

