### Study aim and research question

The aims of this Medical Research Council (MRC) framework phase II trial [27] were translated into the following research question:1.Does the TALKING TIME intervention positively affect the health-related quality of life (HRQoL) of informal caregivers of people with dementia, their perceived social support, and the reaction of the informal caregivers?

To detect possible types of intervention harm for care recipients, a second research question asks the following:2.Does the TALKING TIME intervention affect the challenging behavior of people with dementia who are cared for by an informal caregiver?

Two research questions target the investigation of the study and intervention processes (process evaluation):3.To what extent can the intervention be delivered as planned (degree of implementation)?4.What are the facilitators of and barriers to the TALKING TIME intervention?

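### The primary MCS model adjusts for the secondary outcomes, which the intervention is meant to change, so it does not estimate the effect of assignment

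*Protocol article*

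**What the plan says.** Protocol article, Data analysis, Effect analysis. A mixed model compares the arms on the primary outcome and all secondary outcomes, and intention to treat is invoked in order to estimate the effect of assignment. All effect estimates are to be adjusted for baseline differences and, as a separate item, for control variables at every time point. Then comes: "The mixed effect model for the primary outcome will also consider the secondary outcomes as control variables".

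Table 1 lists the SF-12 physical component summary (PCS), perceived social support (PSSC), caregiver reaction (CRS) and NPI-Q as secondary outcomes, each measured at T0 and T1. The Effect evaluation section also names social conflict (SCS) as a secondary outcome, whereas Table 1 calls it a control variable.

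The protocol treats these variables as things the intervention can change:

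- Background, on the health consequences of caregiving: "These negative consequences can be prevented by interventions that improve the individual coping abilities and perceived social support of informal caregivers".
- Study aim and research question: the first question covers social support and caregiver reaction alongside quality of life. The second asks: "Does the TALKING TIME intervention affect the challenging behavior of people with dementia who are cared for by an informal caregiver".
- Intervention group: the care recipient's behaviour is said to depend possibly on the caregiver's behaviour.

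The sample size rests on the unconditional group difference in MCS: "We assume a more conservative effect size of 0.70".

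**The concern.** A covariate measured after randomisation and changed by treatment is not a neutral adjuster. Conditioning on it does two things.

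1. It takes out whatever part of the treatment effect runs through that variable. If better support or lower burden is how the groups improve mental health, the model subtracts the mechanism from the result.
2. It compares participants who have the same T1 support but come from different arms. They are no longer exchangeable, so any unmeasured common cause of support and mental health biases the group coefficient. Randomisation does not protect against this.

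The physical score is a particularly poor covariate, because it comes from the same SF-12, answered in the same interview, as MCS.

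At stake is the single primary estimate, which the Discussion says will inform a phase III trial. A working intervention could look null, and a neutral one could look harmful.

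**Working it through.** **1. The plan's own figure.** Inputs from Sample size calculation: d = 0.70, two-sided α = 0.05, power 80%, 1:1 allocation. The two-sample t-test needs 33.02 per arm, hence 34 per arm and 68 in total, as stated. Dropout: 34/0.8 = 42.5, rounded up to 43 per arm, gives 86. Rounding up to groups of eight gives 88. Power at 34 per arm is 81%. The sample size is therefore consistent, and it is powered for the total effect on MCS with no allowance for conditioning on other outcomes.

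**2. What the adjusted model estimates.** Take one T1 mediator M and standardise M and MCS to a within-arm SD of 1. Let

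- T = total effect on MCS
- a = effect of assignment on M
- b = slope of MCS on M
- u = loading of an unmeasured common cause on both M and MCS

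The group coefficient after adjusting for M is

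θ = T − a·b − a·u²

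The term a·b is the mediated part. The term a·u² is the bias from the common cause. With n per arm,

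SE ≈ √(1 − (b + u²)²) × √(2/n + a²/(2n))

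The first factor is the precision gained from the covariate. The second includes the cost of M being correlated with arm.

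**3. Numbers.** n = 34 and T = 0.70. The values of a, b and u are assumptions, because the documents give none.

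| a | b | u | Share mediated (a·b/T) | θ | SE | Power |
|---|---|---|---|---|---|---|
| not adjusted | – | – | – | 0.70 | – | 81% |
| 0.2 | 0.50 | 0 | 14% | 0.60 | 0.211 | 80% |
| 0.3 | 0.50 | 0 | 21% | 0.55 | 0.212 | 72% |
| 0.5 | 0.50 | 0 | 36% | 0.45 | 0.217 | 53% |
| 0.7 | 0.50 | 0 | 50% | 0.35 | 0.223 | 34% |
| 0.7 | 0.25 | 0 | 25% | 0.525 | 0.249 | 55% |
| 0.7 | 0.25 | 0.4 | 25% | 0.41 | 0.234 | 41% |
| 0.7 | 0.50 | 0.4 | 50% | 0.24 | 0.193 | 23% |

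Example, fourth adjusted row: θ = 0.70 − 0.7 × 0.5 = 0.35. SE = √0.75 × √(2/34 + 0.49/68) = 0.866 × 0.257 = 0.223. The ratio is 1.57, which gives 34% power.

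**4. No true effect on MCS** (T = 0, b = 0, u = 0.5), so θ = −0.25a:

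| a | θ | Rejection rate (nominal 5%) |
|---|---|---|
| 0.2 | −0.05 | 5.5% |
| 0.3 | −0.075 | 6% |
| 0.5 | −0.125 | 8% |
| 0.7 | −0.175 | 11% |

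Simulated trials with 34 or 35 per arm agree with these formulas to within about two percentage points.

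**5. Direction.** If assignment moved the mediator the wrong way (a = −0.5, b = 0.5), then θ = 0.70 + 0.25 = 0.95, which is inflation. Attenuation is what the protocol's own outcome model predicts, but the sign is not guaranteed.

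**The case against.** **The sentence does not say T1.** This is the strongest point. If only T0 values of the secondary outcomes were meant, the bias disappears. That reading is strained: the sentence calls these outcomes control variables directly after stating that control variables are adjusted for at every time point, baseline differences are listed separately, and nothing restricts the timing or labels the model as mediation. What stands is that the T1 reading is inferred from adjacent text. On either reading the wording has to change.

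**Social support may not be the route.** The Background also describes caregivers' resources as moderators, and reports that earlier telephone interventions showed no effect on social support, which it explains partly by the instruments used. If support hardly moves, adjusting for it does little. But burden, which the Background says telephone groups do affect, is covered by CRS and is in the same covariate set.

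**The loss could be small.** This is correct for small mediator shifts: at 0.2 SD power is barely affected and the type I error stays near 5.5%. The estimate is still shifted, to 0.60.

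**The calculation leaves out baseline MCS.** Also correct. With an assumed baseline correlation of 0.5 (and a mediator shift of 0.7 SD), unadjusted power is about 91%, and the 25% and 50% mediated cases give about 64% to 67% and 45% to 46%. The absolute powers are higher, but the loss remains.

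**Covariates do not breach intention to treat.** Right as a matter of terms: participants are still analysed as randomised. The accurate charge is that the coefficient is not the total effect of assignment, which the plan says it wants.

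**Conclusion.** The concern holds as the text is written. The primary model conditions on variables that the trial itself tests as effects of the intervention, while the same paragraph aims at the effect of assignment. The two cannot both be met.

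The size cannot be derived from the documents. With one mediator and 34 per arm, it runs from negligible power loss (mediator shift 0.2 SD) to an estimate of half the true effect with 34% power (shift 0.7 SD, 50% mediated), and to 23% power if a common cause is added. In the null case the type I error runs from about 5.5% to 11%. The plan adjusts for several such outcomes together, which a single-mediator calculation does not capture. Because the bias can go either way, the result could not be defended as merely conservative. The point must be fixed before unblinding.

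**What to change.** - Remove the sentence that adds the secondary outcomes to the primary model, or restrict it explicitly to their T0 values.
- Change the preceding sentence so that control variables enter at T0 only. Otherwise the same fault remains through the T1 values of GPCOG, FAQ and SCS. Settle whether SCS is a control variable or a secondary outcome.
- State the primary model as: arm, time, arm by time (or T1 MCS adjusted for T0 MCS), the randomisation group of eight, and a short pre-named list of baseline covariates. Use the same rule for every secondary outcome.
- If the role of support or burden is of interest, specify a separate mediation analysis, labelled exploratory, with its assumptions on confounding stated.

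The cost is a few lines of analysis wording before unblinding. No new data are needed, and the sample size of 88 stands, because it was computed for the total effect that the corrected model estimates.
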